**Intervention**

*CS-ADL*

The intervention group will receive a program of CS-ADL, with sessions delivered once weekly across 7 weeks. Typical CST programs commonly delivered by Irish occupational therapy services span a duration of 7 weeks, demonstrating that an intervention of this length is feasible within these services. CS-ADL sessions will last approximately 2 hours. While Ryan and Brady’s (2023) scoping review reported significant ADL benefits from the intensive multi-component CS interventions of Graessel et al. (2011) and Muñiz et al. (2015), Jiménez Palomares et al.’s (2021) occupational therapy CS program reported benefits for ADLs through a less intensive approach of two 45-minute sessions per week for a total of 5 weeks. As typical community-based CST programs often deliver two 45-minute sessions on the one day to aid feasibility, the planned intensity and duration of the CS-ADL program is therefore justified. At least one qualified occupational therapist will facilitate the sessions, with the assistance of a co-facilitator, as CS-ADL activities require a level of supervision not feasible for a single facilitator. Furthermore, the lead group facilitator must be an occupational therapist as the aims of CS-ADL align with the core principles of the profession. Each session consists of similar components, however the sequence and timing allocated per component may differ between sessions. Activities are based around a different theme for each session, for example morning routine, evening routine, or domestic activities, with each session intended to be enjoyable and mentally stimulating for the individual. A typical session will begin with 20-minutes of introductions, reality orientation, a group song and discussion of the news of the week. 15-minutes will then be spent on a physical activity/game. Physical activity will be a key component of the CS-ADL program as 7 of 9 CS programs reviewed by Ryan and Brady (2023) involving a physical activity component to intervention reported benefits for ADL outcomes. A physical activity at the start of the group will also aim to benefit arousal levels of participants and build rapport amongst group members. This will be followed by 25-minutes of ADL-focused cognitive stimulation activities, a 15-minute break, and approximately 10 more minutes of ADL-focused CS activities. These activities will include the identification and categorisation of everyday items, discussion, reminiscence, planning and sequencing of ADLs and the completion of everyday writing/calculation tasks. This will be followed by a 30-minute ADL task, which is an essential component to the program, as Ryan and Brady’s (2023) review found CS interventions with an ADL component report significant benefits for ADL outcomes. Examples of activities will include making a breakfast, a simple gardening activity or sorting laundry. While the structure of CS-ADL has taken inspiration from previous CS programs (Graessel et al., 2011; Jiménez Palomares et al., 2021; Spector et al., 2003), CS-ADL differs as participants are actively engaged in the planning, preparation, and practice of everyday activities like washing, dressing, and cooking. A full groupwork protocol and detailed session plans are available at Appendix 1 and Appendix 2.1 respectively. Sample handouts and instructional cards used in the implementation of CS-ADL sessions are available from appendix 2.2 to appendix 2.8. Therapists involved in the administration of CS-ADL are advised to use their clinical judgement in the planning and implementation of sessions, as sessions should be individualised to suit the needs, abilities, and interests of group members. Activities should be adapted accordingly.

*Treatment-as-usual*

The control group will continue to have access to treatment as usual, which will include medication, input from health professionals and any activities provided in the day hospital if the participant is in attendance. After the completion of the study, participants and their caregivers will be offered a home programme based on the CS-ADL intervention and will be given training in how to use it.

*Outcome measures*

Outcome measures will be recorded in both CS-ADL and TAU participants at baseline (week 0) and post-intervention (week 8). The completion of outcome measures pre- and post-intervention will be mandatory for participation in the trial; participants and caregivers will be reminded of requirements prior to the commencement of the group and after the completion. Socio-demographic information of participants will be collected including age, gender, ethnicity, diagnosis, and medication.

*Primary outcomes: BADL and IADL*

Change in both BADL and IADL will be measured using the Alzheimer's Disease Cooperative Study-Activities of Daily Living (ADCS-ADL) scale (Galasko et al., 1997). This scale was designed for the assessment of ADL outcomes for individuals with Alzheimer's disease in clinical trials. The scale consists of 23 items that includes 6 BADL and 17 IADL outcomes, scored on a range from 0 (patient does not perform the activity), to the highest score (patient is independent in the activity). The scale is administered with caregivers who are asked to rate the degree to which their care-recipient performs each item in the last four weeks (Custodio et al., 2022). The ADCS-ADL has been identified to be a reliable and valid instrument, with high internal consistency and sensitivity to functional changes in individuals with mild-to-moderate dementia (Rózsa et al., 2009).

*Secondary outcomes: Cognition, communication, QOL, mood.*

General cognitive functioning will be measured using either the Montreal Cognitive Assessment (MoCA) face-to-face or the MoCA-Blind delivered via the telephone, dependent on feasibility for participants and assessors. The MoCA is a brief screening tool used to detect cognitive impairment and consists of a 30-point test assessing the cognitive domains of visuospatial/executive, naming, memory, attention, language, abstraction, delayed recall, and orientation. The MoCA exhibits high sensitivity and specificity and its validity for use with people living with dementia (PLwD) has been well established (Nasreddine et al., 2005). The MoCA-Blind does not require visual input and was developed to enable cognitive screening of those with visual impairment, also enabling administration through telephone or online formats. The MoCA-Blind is scored on a scale of 22 points as visual elements are excluded. While specificity remains on par with the original MoCA, sensitivity is reduced (Wittich et al., 2010).

Cognition will be assessed using the Repeatable Battery for Assessment of Neuropsychological Status (RBANS; Randolph, 1998). The RBANS is a commonly used brief battery of cognitive function for individuals with dementia. This battery consists of 12 subtests which assess five cognitive domains: immediate memory, visuospatial-constructional ability, language and delayed memory. This battery has demonstrated good reliability and adequate validity indicators (Shura et al., 2018).

Communication ability will be assessed using the Holden Communication Scale (HCS; Holden and Woods, 1995). This scale includes 12 items assessing the domains of conversation, awareness, humour, and responsiveness. Each items contains five response options ranging from 0 to 4. Total scores can range from 0 to 48 with higher scores indicating more communication difficulties. The HCS was initially developed to assess communication outcomes in reality orientation and reminiscence programs and has demonstrated good reliability and validity for use with PLwD (Strøm et al., 2016). While there are limitations to reliability and validity data outside of the original development of the tool (Dolan and Shiel, 2017), the HCS has been used in various CS studies to assess communication (e.g., Orrell et al., 2005; Spector et al., 2003).

QOL will be assessed using the Quality of Life-Alzheimer’s Disease Scale (QOL-AD). This scale consists of 13 items spanning the domains of physical health, energy, mood, living situation, memory, family, marriage, friends, chores, fun, money, self, and life as a whole. Response options include 1 (poor), 2 (fair), 3 (good) and 4 (excellent), with total scores ranging from 13-52. Assessment is delivered through an interview format and separate ratings are obtained from the participant themselves and the caregiver. Higher scores indicate a better quality of life. The QOL-AD has demonstrated good reliability and internal consistency (Logsden et al., 1999) and has been found to detect improvements in QOL in previous CS studies (Orrell et al., 2014; Spector et al., 2003).

Mood will be assessed through the presence of neuropsychiatric symptoms as measured by the Neuropsychiatric Inventory Questionnaire (NPI-Q), a version of the Neuropsychiatric Inventory (NPI; Kaufer et al., 1998). The NPI-Q is a caregiver-based questionnaire that measures the presence and severity of 12 neuropsychiatric symptoms in PLwD, including delusions, hallucinations, apathy, disinhibition, and agitation/aggression. The severity scale runs from 1 to 3 points (1=mild, 2=moderate, 3=severe). The questionnaire also measures the respective level of caregiver distress associated with each symptom, with the scale running from 0 to 5 points (0=no distress, 5=extreme distress). The scale is widely used in research, has demonstrated acceptable levels of internal consistency, and has been cross validated with the standard NPI in clinical practice settings (Cummings, 1994).

*Other outcome measures*

Occupational performance within a group setting will be measured after each session using the Occupational Therapy Task Observation Scale (OTTOS). The OTTOS contains two parts, with 10 items for evaluation of specific task functions and 5 items for rating general behaviour. The reliability and validity of the OTTOS has been demonstrated (Margolis et al., 1996).

*Statistical analysis*

The study sample will be analysed using descriptive statistics through the latest version of Statistical Package for Social Sciences (SPSS). Data on recruitment will be recorded and examined. A Consolidated Standards of Reporting Trials (CONSORT) diagram describing the flow of participants through the study will be presented in the final RCT report, detailing enrolment, allocation, follow-up, and analysis of data (Figure 1). Baseline data will be assessed for normality and if normally distributed, parametric analysis will be used. Where data is not normally distributed, non-parametric analysis will be used. Types of tests chosen will be based on whether the data is parametric or non-parametric. Significance levels will be set to 0.05. A linear regression model adjusting for baseline scores will be used to estimate the effect of intervention on each of the primary and secondary outcomes, with a between-group analysis completed to examine if the groups are significantly different at outcome. A within-group analysis will be also completed to evaluate if there are any significant changes within groups. Sociodemographic factors like age and gender will be entered as covariates.

*Ethical considerations*

The researchers are currently in the process of receiving ethical approval for this study.

*Anticipated risks for trial participants*

There appear to be no documented harmful side effects from participating in typical CS programs, with no adverse reactions apparent. Health and safety risks, including the risk of falls may be posed by the participation in cooking tasks and physical activities. However, group facilitators will use their clinical judgement, clinical risk assessments in the implementation of activities and always ensure adequate supervision is given. Nevertheless, potential participants and their caregivers will be fully informed of the potential risks before partaking in the trial.

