| **Outcome measures** | Primary outcomes of the group will be basic ADL (BADL) and instrumental ADL (IADL) outcomes.  -The Alzheimer’s Disease Co-operative Study – Activities of Daily Living (ADCS-ADL) will be used to measure BADL and IADL outcomes.  Secondary outcomes will be cognition, communication, mood, and quality of life.  -Cognition is a secondary outcome of this group and general cognitive functioning will be measured using the Montreal Cognitive Assessment (MoCA) or MoCA-Blind via telephone, dependent on feasibility for participants or the assessor. Cognitive functioning will be assessed using the Repeatable Battery for Assessment of Neuropsychological Status (RBANS). This battery assesses five cognitive domains: immediate memory, visuospatial-constructional ability, language and delayed memory.  -Communication ability will be measured using the Holden Communication Scale (HCS).  -Quality of life will be assessed using the Quality of Life-Alzheimer’s Disease Scale (QOL-AD).  -Mood will be assessed through the presence of neuropsychiatric symptoms as measured by the neuropsychiatric inventory questionnaire (NPI-Q). |
| **Referral criteria** | Please refer to eligibility criteria. Local occupational therapy referral protocols to be followed. |

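### General cognition may be scored on a 30-point or a 22-point test, with no rule to keep one version per participant or to use a common score; this costs precision and, if telephone use differs by arm, creates a false difference.

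*Protocol*

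**What the plan says.** Under the heading on secondary outcomes, the protocol assesses general cognition with "either the Montreal Cognitive Assessment (MoCA) face-to-face or the MoCA-Blind delivered via the telephone, dependent on feasibility for participants and assessors". The MoCA "consists of a 30-point test assessing the cognitive domains" that the section lists. For the telephone version it states: "The MoCA-Blind is scored on a scale of 22 points as visual elements are excluded". It adds that the two do not perform alike: "While specificity remains on par with the original MoCA, sensitivity is reduced". The outcome-measures row of Appendix 1 repeats the choice: "Montreal Cognitive Assessment (MoCA) or MoCA-Blind via telephone, dependent on feasibility for participants or the assessor".

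Outcomes are taken in both arms at week 0, before randomisation, and at week 8. The Statistical analysis section plans, for each primary and secondary outcome, a linear regression on arm with the baseline score as covariate, and also tests of change within each group. The covariates it names are sociodemographic, with age and gender as examples. The protocol does not require the same version at both visits, convert the two versions to one scale, or adjust for version.

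**The concern.** A change from one version to the other between visits moves the score with no change in the person. Baseline adjustment does not remove this, because the covariate and the response are then on different scales. The same problem reaches the within-group tests, where a net shift towards the telephone between visits looks like decline.

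Three consequences need to be kept apart:

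- Random mixing that is equal in both arms adds noise to a comparison of 34 people.
- A net shift in version between visits distorts the within-group change, whatever happens in the other arm.
- An arm difference in telephone use at week 8 biases the between-group estimate. The week-8 version is chosen after randomisation, so the design does not exclude this.

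**Working it through.** **Inputs from the protocol.** Maxima of 30 and 22 points (secondary outcomes section), so 30 − 22 = 8 points are removed. Sample size 34 with 1:1 allocation (Trial design), so 34 / 2 = 17 per arm. Two-sided alpha 0.05. The stated power of 0.8077775 for 34 reproduces as 0.8078 for a matched-pairs t-test at d = 0.5. That figure is not at issue here; only the 34 is used.

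**Assumptions not in the protocol.** A MoCA-Blind score equals 22/30 of the same person's MoCA score (pro rata). MoCA between 12 and 21. For the simulation: mean 16, SD 4, correlation 0.8 between visits.

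**Step 1, artefact in one person who changes version.** Artefact = MoCA × (1 − 22/30) = MoCA × 8/30.

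| MoCA | Artefact (points) |
|---|---|
| 12 | 3.2 |
| 15 | 4.0 |
| 18 | 4.8 |
| 21 | 5.6 |

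At 15, for example, 15 × 22/30 = 11, a fall of 4 with no change in cognition.

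**Step 2, within-group change.** Apparent mean change = net share who move to the telephone × artefact. If 30% of one group move, at a MoCA of 15, the group mean falls by 0.30 × 4.0 = 1.2 points.

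**Step 3, between-group difference.** Expected false difference = arm gap in telephone use at week 8 × artefact.

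- Low end: 0.10 × 3.2 = 0.32.
- Middle: 0.30 × 4.0 = 1.2.
- High end: 0.50 × 5.6 = 2.8.
- No gap: 0.

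**Step 4, simulation of the baseline-adjusted regression.** 17 per arm, 20,000 runs, no true effect, assumptions as above. A dash means the figure is not needed for the argument.

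| Use of MoCA-Blind | Mean false difference | Type I error | Standard error |
|---|---|---|---|
| None | 0.0 | 0.051 | 0.84 |
| 30% at random, both arms, both visits | 0.0 | 0.049 | 1.15 |
| 30% in both arms, fixed within person | 0.0 | 0.050 | – |
| None at baseline; week 8: 10% CS-ADL, 30% TAU | 0.87 | 0.13 | – |
| None at baseline; week 8: 10% CS-ADL, 50% TAU | 1.71 | 0.39 | – |
| 30% in both arms at baseline; week 8: 10% CS-ADL, 50% TAU | 1.71 | 0.32 | – |

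The formula in step 3 agrees. At a mean of 16 the artefact is 16 × 8/30 = 4.27, and 0.20 × 4.27 = 0.85, 0.40 × 4.27 = 1.71.

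**Step 5, cost of equal random mixing.** The variance ratio is (0.84 / 1.15)² = 0.53. In precision that is roughly 0.53 × 34 = 18 participants out of 34. Power for an assumed true effect of 2 points falls from 0.64 to 0.33.

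**Step 6, common 22-point score for all.** Type I error is 0.049 and power for the same assumed effect is 0.64. This run treats the 22-point score as an exact rescaling, so it does not measure what is lost by dropping the visual items.

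**The case against.** The strongest objection is that nothing in the documents shows telephone use differing by arm. CS-ADL sessions end after week 7 and outcomes are taken at week 8, so the intervention arm has no session to attend then. TAU participants may attend the day hospital. Both arms come from the same services, assessors do not know the allocation, outcome completion is mandatory, and the transport funding to be sought is not limited to one arm. This stands. A reader might infer that the rule favours CS-ADL because its participants attend weekly, but the documents support this only as a possibility. Blinding narrows it without closing it, since the choice also rests on feasibility for the participant.

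A second objection is that the rule can be read as one version per participant, in which case the simulated bias is zero. The protocol is silent, so this reading is available but not secured.

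A third is that scoring detail belongs in the SAP. Rescaling of totals or a version covariate could indeed be placed there. The choice of instrument, however, is a data-collection rule fixed in the protocol, and a common-item score needs item-level records planned before the first assessment.

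A reader might also infer that the telephone version is never needed, because the RBANS covers "immediate memory, visuospatial-constructional ability, language and delayed memory" and so implies a visit. The protocol does not say how the RBANS is administered. If it does force a visit in both arms, a large gap in telephone use becomes less likely too.

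**Conclusion.** The point holds as a defect in how one secondary outcome is collected. As written, the plan lets scores on two different maxima enter one regression and one change test. A change of version moves a person's score by about 3 to 6 points, given pro rata scoring and a MoCA of 12 to 21. People who already fail the visual items would move less.

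Loss of precision does not depend on any arm imbalance. Its size rests on the assumed 30% telephone use, mean, SD and correlation. Bias between arms is conditional: about 0.3 to 2.8 points for a gap of 10 to 50 percentage points at week 8, and none without a gap. The protocol gives no telephone rate, so the documents do not show which case applies.

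A reader might take the 8-point difference in maxima as the size of the artefact, and so reach a false difference of 4 points (0.50 × 8). That would need every person who changes version to have full marks on all visual items, which is implausible on average in mild-to-moderate dementia.

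The primary outcome, the ADCS-ADL, and the second cognition measure, the RBANS, are untouched. The change is worth making before data collection, but the main result does not hang on it.

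**What to change.** In the secondary outcomes section and in the outcome-measures row of Appendix 1:

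- Require the same version for a participant at baseline and week 8. Because baseline precedes randomisation, a version fixed then cannot depend on arm.
- Record the MoCA item by item.
- Analyse all participants at both visits on the 22 points from the non-visual items common to both versions, taken from the full MoCA where that was used.
- Prefer face-to-face testing where feasible, but do not make it compulsory; compulsion could cost missing data in a trial of 34.
- Record version and mode at each visit. If a change of version cannot be avoided, keep the person in the analysis on the common score and report the number by arm.

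The membership row of Appendix 1 names the same two versions for screening. The new wording should make clear that it governs the outcome assessments.

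The cost is a few sentences of protocol text and item-level data entry. The score loses its visual items, a domain the RBANS still covers. A common score does not remove any difference between telephone and face-to-face testing itself, which is why the same version within a person comes first.

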The aim of this study is to evaluate the effect of CS-ADL, an ADL-focused multi-component CS program, on ADL outcomes for people living with mild-to-moderate dementia. The primary objective of this study is to determine the effect of CS-ADL on basic ADL (BADL) and instrumental ADL outcomes (IADL). The secondary objectives of the study include examining the effects of the intervention on cognition, mood, quality of life (QOL) and communication. These secondary outcomes were chosen as previous CS programs have demonstrated benefits for these variables (Woods et al., 2012).

*Hypotheses*

*Null hypotheses*

CS-ADL does not benefit ADL outcomes in people with mild-to-moderate dementia when compared to TAU.

CS-ADL does not benefit cognition, mood, quality of life and communication in people with mild-to-moderate dementia when compared to TAU.

H_0_: µ_CS-ADL_ = µ_TAU_

*Alternate hypotheses*

CS-ADL benefits ADL outcomes in people with mild-to-moderate dementia when compared to TAU.

CS-ADL benefits cognition, mood, quality of life and communication in people with mild-to-moderate dementia when compared to TAU.

H_1_: µ_CS-ADL_ > µ_TAU_

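### Mood is a secondary objective and hypothesis, but its measure is the NPI-Q with no restriction to mood symptoms, so the result will support a statement about neuropsychiatric symptoms rather than mood

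*Protocol*

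**What the plan says.** Under Aims and objectives, the protocol states: "The secondary objectives of the study include examining the effects of the intervention on cognition, mood, quality of life (QOL) and communication". The alternate hypothesis under Hypotheses turns this into a directional claim: "CS-ADL benefits cognition, mood, quality of life and communication in people with mild-to-moderate dementia when compared to TAU". Mood is listed again as a secondary outcome in the Abstract, the Discussion and the Outcome measures row of Appendix 1. Benefiting participants' mood is also one of the group goals in Appendix 1.

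The measure is fixed under Secondary outcomes: "Mood will be assessed through the presence of neuropsychiatric symptoms as measured by the Neuropsychiatric Inventory Questionnaire (NPI-Q"). Appendix 1 says the same: "Mood will be assessed through the presence of neuropsychiatric symptoms as measured by the neuropsychiatric inventory questionnaire (NPI-Q").

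The protocol describes the instrument as a caregiver-based questionnaire that "measures the presence and severity of 12 neuropsychiatric symptoms in PLwD, including delusions, hallucinations, apathy, disinhibition, and agitation/aggression". On scoring it adds: "The severity scale runs from 1 to 3 points (1=mild, 2=moderate, 3=severe"). It then notes: "The questionnaire also measures the respective level of caregiver distress associated with each symptom", on a range of 0 to 5.

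The Statistical analysis section applies a baseline-adjusted linear regression to every primary and secondary outcome, mood included.

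**The concern.** The construct in the objective and hypothesis is not the construct that is measured. Mood is one part of what a broad neuropsychiatric inventory may cover, and the protocol treats the presence of any such symptom as an indicator of mood.

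What is at stake is the conclusion the trial may draw. If fewer participants in the CS-ADL arm have delusions or agitation at week 8, the protocol as written would report this as a mood benefit. If those symptoms do not change, it would report no mood benefit, even if participants' mood had improved. Neither statement would follow from the data.

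A mood claim is a realistic end product here. The Introduction cites qualitative work in which mood benefits were reported, and the programme sets out to improve mood.

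**Working it through.** This is a question of construct, so no calculation applies. The protocol's only design calculation is the sample size, which does not bear on the point. The check sets the relevant statements side by side.

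1. **What is to be concluded.** Aims and objectives and Hypotheses refer to mood, in people with dementia, compared with treatment as usual.

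2. **What is to be measured.** Secondary outcomes and Appendix 1 (Outcome measures row) both refer to the presence of neuropsychiatric symptoms on the NPI-Q. Neither names a subset of symptoms.

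3. **What the NPI-Q contains, on the protocol's own account.** It has 12 symptoms, of which five are named.

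| Named symptom | Kind |
| --- | --- |
| Delusions | Psychotic |
| Hallucinations | Psychotic |
| Disinhibition | Behavioural |
| Agitation/aggression | Behavioural |
| Apathy | Neither of these, but not depressed or anxious mood |

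   The other 12 − 5 = 7 symptoms are not listed. Some of them may concern mood, but the document does not say which or how many.

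4. **Whether mood is captured elsewhere.** Among the outcome instruments described, the only other mention of mood is as one of the 13 QOL-AD domains, rated separately by participant and caregiver. That scale is assigned to quality of life, and no separate use of its mood item is planned. The protocol contains no dedicated mood scale.

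5. **What follows.** At least four of the 12 symptoms can change without any change in mood, and nothing in the definition sets them aside. A between-group difference on the measure as defined is therefore compatible with better, worse or unchanged mood. The inference it supports concerns neuropsychiatric symptoms.

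Step 5 needs no assumption about the seven unlisted symptoms. It holds even if several of them are mood symptoms, because the definition does not separate them from the rest.

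**The case against.** The strongest reply is that the protocol states its operational definition openly and in the same terms in both places. There is no contradiction, and a careful reader can see what mood means here. Using a broad inventory as a proxy is partly a design choice, and the protocol cites evidence of internal consistency and of agreement with the standard inventory. The openness is a fair point and keeps the matter small. The cited evidence, however, supports the NPI-Q as a measure of neuropsychiatric symptoms. It does not make the result a measure of mood, and the hypothesis would be read and reported under the word mood.

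A second reply is that the statistical analysis plan, which is not shown, may choose the NPI-Q score. That is right as far as it goes: whether presence or severity is analysed, and how an absent symptom is scored, can properly be left there. But the objective, the hypothesis and the definition of the outcome are protocol content, and the mismatch lies in them.

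Two stronger readings are tempting, and the document does not support either.

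- A reader might infer that caregiver distress will be counted as participant mood. The protocol defines mood through the presence of symptoms. It mentions distress only as something the form also records, and nowhere assigns it to mood or adds it to severity. Its use is left open rather than planned.
- A reader might infer that a true mood effect would be diluted by some calculable amount. Any such figure needs the number of mood symptoms and their correlation with the others. The document lists only five of the 12 symptoms and gives no correlations.

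Finally, some participant-reported information on mood is collected through the QOL-AD. That is true and should be acknowledged, but it is a single item within a different outcome.

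**Conclusion.** The concern holds as a mismatch between label and measure. As written, the trial would state a conclusion about mood from a measure that, on the protocol's own description, also moves with delusions, hallucinations, disinhibition and agitation. The supportable conclusion concerns neuropsychiatric symptoms.

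The size is modest: one of four secondary domains (cognition, mood, quality of life, communication). The primary ADL outcome, its analysis, the sample size and the randomisation are unaffected. No numerical bias is claimed.

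The verdict rests on the protocol's description of the NPI-Q and on reading delusions, hallucinations, disinhibition and agitation/aggression as not being mood. It assumes nothing about the unlisted symptoms or about which NPI-Q score will be analysed.

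**What to change.** 1. In the Abstract, Aims and objectives, Hypotheses (null and alternate), Secondary outcomes, Discussion and the Outcome measures row of Appendix 1, replace mood as the outcome with *neuropsychiatric symptoms (NPI-Q)*. The group goal of benefiting mood in Appendix 1 can stay as an aim of the programme.
2. Base any statement about mood only on those NPI-Q symptoms that concern mood. Take them from the same completed form and name them before unblinding. If the form holds none that the investigators would accept as mood, make no mood statement.
3. State that the caregiver-distress rating, if analysed, is a caregiver outcome and not part of participant mood.

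The cost is a change of wording and, if wanted, one more score derived from data already collected; participants and caregivers do nothing extra. The protocol says ethical approval is still being sought, so the change is easiest now. The real downside is that mood ceases to be a headline secondary objective, and any remaining mood claim is narrower and rests on few items. If the sponsor wants mood kept as an objective in its own right, the alternative is to add a dedicated mood scale, which would add an assessment at both time points.
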